## Abstract

**Background:**

Frequent hospitalization and permanent nursing home placement not only affect the well-being of persons with dementia, but also place great financial strain on society. Therefore, it is important to create effective strategies to support informal caregivers so that they can continue to perform their demanding role. Preliminary qualitative evidence suggests that community-based respite services can actually be important for caregivers, and that the level of evidence should be further established in terms of effectiveness. Therefore, a comparative study to assess the effectiveness and cost-effectiveness of an in-home respite care program will be initiated.

**Methods:**

This manuscript described a quasi-experimental study to assess (cost)-effectiveness of an in-home respite care program to support informal caregivers of persons with dementia. Study population: 124 informal caregivers and persons with dementia will be included in the intervention group and will receive an in-home respite care program by an organization called Baluchon Alzheimer. 248 dyads will be included in the control group and will receive standard dementia care. The primary outcome is caregiver burden. Secondary outcomes are: quality of life of caregivers, frequency of behavioral problems of persons with dementia and the reactions of caregivers to those problems, intention to institutionalize the care-recipient, time to nursing home placement, resource use of the care-recipient, and willingness to pay for in-home respite care. When the trial demonstrates a difference in outcomes between both groups, within-trial and modeled cost-effectiveness analyses will be conducted in a separate economic evaluation plan to evaluate possible cost-effectiveness of the in-home respite care program compared to the control group receiving standard dementia care. Finally, the model based cost-effectiveness analyses will allow to extrapolate effects over a longer time horizon than the duration of the trial.

**Discussion:**

This study will have great added value because to date no studies measured effectiveness and cost-effectiveness of an in-home respite care program of the Baluchon type. Results of this trial can thus give much more insight in potential benefits and disadvantages of community-based respite care. Conclusions based on this trial can help policy-makers in elaborating future directions of dementia care.

**Trial registration:**

Clinicaltrials.gov Identifier NCT02630446.

## Background

Dementia is a known major public health problem with serious physical and emotional consequences for patients and their caregivers, and a high financial strain upon society. Knowing that on the one hand staying in the community may result in more quality of life for the patient and on the other hand there is a high cost of the disease for the society due to frequent hospitalization and permanent institutionalization in nursing homes, it can be stated that informal caregivers are essential in the care process and probably cost saving for society [1–7].

Although caregiving for a loved one can be very satisfying, it also demands a lot from informal caregivers over long periods due to the progressive decline of the disease [5, 8]. Most research of the past decade has shown that informal caregivers have more health problems, visit healthcare professionals more frequently, suffer from isolation, and have an increased risk of depression, distress and other illness [1, 2, 6, 8–12]. To prevent caregivers from getting overburdened, different supportive interventions, such as psychoeducation have been developed to improve their well-being.

Based on a recently conducted systematic review of comparative studies (randomized controlled trials and quasi-experimental studies), it was concluded that supporting caregivers is an effective strategy in improving well-being of caregivers and their recipients resulting in additional benefits for society. It also appeared that considerable research was done in investigating effectiveness of psychoeducational interventions, cognitive behavioral therapy, and occupational therapy, but research on the comparative effectiveness of respite care - which can be defined as a supportive service provided in or outside the home to give the informal caregiver a temporary relieve or beak from caregiving duties - was very rare [13].

An additional review, that also allowed observational designs without control group, was conducted to investigate the effectiveness of different types of respite care. In this review it was concluded that day care services are effective in decreasing caregiver burden and behavioral problems in people with dementia, but also accelerate time to nursing home placement. Results of temporary residential admission were rather mixed and showed unexpected adverse effects on both caregivers and care-recipients. No comparable evidence was found for night-time care in residential settings. Evidence on community-based respite care, including in-home respite care and host family respite care, is rare as well. Only one in-home respite care intervention was identified indicating some benefits for caregivers. Finally, there was no research on cost-effectiveness of any of the investigated types of respite care. As a result, the authors concluded that there is a need for new intervention studies measuring effectiveness and investigating cost-effectiveness of respite care. Especially the effect of an in-home respite program on the caregiver, the care-recipient, and the healthcare system should be further investigated [14].

On the other hand, substantial qualitative research indicated high satisfaction and positive perceptions regarding respite care in general and pointed out that breaks are crucial if caregivers are to continue to keep their loved ones home. Additionally, many caregivers pointed out their preference for in-home respite care, especially because in this way their loved ones can stay in their trusted environment [14].

Because current evidence suggests that respite services can actually be important and effective strategies for caregivers, but that the level of evidence should be further established in terms of effectiveness, especially for in-home respite care, we designed a quasi-experimental study to assess the effectiveness of an in-home respite care program compared to a control group not receiving the same type of in-home respite on the well-being of the caregiver, the care-recipient, and on the healthcare system. The latter in terms of resource use, intention to institutionalize the care-recipient, and time to nursing home placement.

When the trial demonstrates a difference in outcomes between both groups within-trial and modeled cost-effectiveness analyses will be conducted in a separate economic evaluation plan to evaluate possible cost-effectiveness of the in-home respite care program compared to the control group receiving standard dementia care. Finally, the model based cost-effectiveness analyses will allow to extrapolate effects over a longer time horizon than the duration of the trial.

The specific research questions to be answered are:Is in-home respite care an effective strategy in supporting informal caregivers of people with dementia? Can in-home respite care decrease their burden, improve their reactions to behavioral problems and cause a difference in quality of life of the caregiver?What impact does in-home respite care have on the frequency of behavioral problems of people with dementia?What impact does in-home respite care have on the healthcare system in terms of resource use, intention to institutionalize, and time to nursing home admission?Is in-home respite care a cost-effective strategy in supporting informal caregivers of people with dementia from the healthcare payer and societal perspective compared to no in-home respite care?What are informal caregivers of persons with dementia willing to pay per day for in-home respite care?

## Methods/design

### Design

A quasi-experimental study is designed to assess the effectiveness of an in-home respite care program on caregivers of persons with dementia. The intervention group will consist of caregiver/care-recipient dyads receiving an in-home respite program called “Baluchonnage” and will be compared to a control group that does not receive this program. Comparison between the groups will be done by collecting health related and economic data.

Eventually, if the intervention is effective, modeled and trial based cost-effectiveness analyses will be undertaken in a separate economic evaluation plan. Analyses will be performed from the perspective of the healthcare payer (RIZIV/INAMI (National Institute for Health and Disability Insurance) and patient) and from a full societal viewpoint. Finally, the model based cost-effectiveness analyses will allow to project effects over a longer time horizon than the duration of the trial. An additional five-years’ time-horizon is chosen based on evidence of the average life expectancy in dementia [15, 16].

### Study participants

The study participants are caregiver/care-recipient dyads. The caregivers must be informal, meaning that they must not be professional healthcare workers in this caregiving role. They have to identify themselves as the main person responsible for the informal care (primary caregiver). Also, they must speak Dutch or French with some fluency and be able to read and write. Finally, caregivers will be excluded if they have cognitive impairments or severe psychiatric comorbidities. The care-recipient needs to be diagnosed with dementia and must live in the community. Evidence of symptoms will also be confirmed by testing for severity (Global Deterioration Scale) [17]. Finally, dyads of the control group must never had in-home respite of the Baluchon type, but be eligible and willing to receive it. On the other hand, dyads from the intervention group who have already received in-home respite care from the Baluchon type in the past are still allowed for inclusion in the intervention group.

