Medication use dementia-specific CR	X		X	
Earlier use of Baluchon	X			
Preparedness to receive in-home respite	X			
Reason for respite			X	
Time spent in caregiving	X		X	
Severity of dementia CR	X		X	
ADL functioning CR	X		X	
Research outcomes				
Quality of life of CG	X		X	
Burden of CG	X		X	X
Frequency of behavioral problems of CR	X		X	
Reaction of CG on behavioral problems of CR	X		X	
Intention to institutionalize the CR	X		X	X
Resource use CR	X		X	
Willingness to pay			X	
Time to nursing home placement CR				X

*CG* Caregiver, *CR* care-recipient, *ADL* Activities of Daily Living

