### Background characteristics

For caregivers we will obtain the following background characteristics: age, gender, region, marital status, ethnicity, educational level, relationship with the care-recipient, employment status, living situation, and time spent in caregiving. In both study groups the reason for (potential) use of respite will be asked based on evidence from the study of Connell et al. (2012) [30]. Earlier use of Baluchonnage will also be questioned to intervention group participants (Tables 1 and 2).

For the care-recipient the following background characteristics will be collected: age, gender, marital status, ethnicity, region, National Registration Number, educational level, being on a waiting list for long-term nursing home placement, dementia-specific medication use, activities of daily living (Belgian Katz scale), and severity of dementia (GDS). In a later phase, the National Registration Number of the person with dementia will allow us to trace study participants in the IMA database (Intermutualistisch Agentschap) and gather information on resource use and date of placement in a nursing home over a longer time period than the trial (Tables 1 and 2).

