### Statistical analysis

First of all, descriptive statistics will be represented to draw a clear profile of the characteristics of study participants. Therefore the mean, percentages, and the standard deviations of quantitative variables will be displayed. To determine possible baseline differences between the groups, mean values of baseline characteristics will be compared using independent sample t-tests for continuous variables if normally distributed or by performing Pearson’s chi-square test for categorical variables. To help control for bias and confounding, statistical techniques such as propensity score matching will be used. Propensity score matching can be seen as a tool to simulate a RCT setting. In this way we can expect the observed effect to be an unbiased estimate of the real effect [41, 42].

To investigate possible effects of the intervention on the primary and secondary outcomes, analysis of variance will be conducted if the outcome variables are normally distributed. A *P*-value of 0.05 will be considered as significant. All analyses will be based on intention to treat also taking drop-outs into account and avoiding overestimation of respite care effects.

When the intervention is effective a cost-effectiveness analysis in a separate economic evaluation plan will be performed. ICERs will be calculated for the mean and upper and lower confidence levels of the costs and consequences. To explore uncertainty one-way-sensitivity analysis will be conducted around the ICER and illustrated in a Tornado diagram. Additionally, on all input variables a probabilistic sensitivity analysis, also called Monte Carlo analysis, will be conducted to test robustness of the model. These results will also be illustrated. Finally, the results and the willingness to pay threshold of the Belgian Health Care System will be presented in a cost-effectiveness acceptability curve [34].

To compare time to nursing home placement of persons who use respite care to those who do not, we will use Kaplan-Meier survival curves to illustrate association between the comparison groups. By additionally conducting a log-rank test statistical difference between the groups in time to placement can be found [43].

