## Discussion

A first major strength of this trial is its contribution to the need for evidence on effectiveness and cost-effectiveness of in-home respite care. To date no other studies measured effectiveness and cost-effectiveness of an in-home respite service similar to the Baluchon service. Findings of this trial can also contribute to the elaboration of future directions of healthcare policies. After all, if in-home respite is effective in supporting informal caregivers and also cost-effective, policy makers should consider reimbursement of in-home respite care.

This trial has several methodological strengths often lacking in previous research. First of all, this study only uses international, validated, and widely used measurement tools to measure the research outcomes. Also, to better adapt some instruments to the Belgian context and this trial, adjustments were made for some instruments. When no valid translation in Dutch of French for Belgium was present we used a proper forward-back translation technique. Secondly, we performed a sample size calculation to know the necessary amount of caregivers needed to show an effect in the primary outcome given a certain effect size. In this analysis we also took into account an average drop-out rate to be expected. Additionally, intention-to-treat will be used to take into account drop-outs. To avoid bias and confounding, often occurring in non-randomized controlled trials, we will use propensity-score matching to simulate an RCT setting. In this way, the found intervention effects can be considered unbiased estimates of the real effect. Finally, active components of the intervention are clearly described, reasons for drop-out will be documented and characteristics of drop-out participants will be compared to those who completed the trial.

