Despite the promising contribution of this study to community-based dementia care, several limitations need to be mentioned as well. First, there is a threat towards internal validity because the used quasi-experimental study design lacks random assignment of study groups. Although we use inclusion criteria to increase comparability and statistical efforts such as propensity score matching will be untaken, there can still be unmeasured confounders influencing causal inference. Nevertheless, for this particular research, a quasi-experimental design was preferable over a randomized controlled trial for feasibility and ethical reasons. First of all, the limited capacity of Baluchon Alzheimer Belgium makes it impossible to set up a RCT. Also, it can be seen as ethically unacceptable to randomly assign dyads to one of the trials arms. In this way some caregivers get free respite care while others cannot have this support during the trial.

Second, we only recruited caregivers asking for in-home respite care themselves in the intervention group and caregivers prepared to utilize this service in the control group. Therefore we cannot speculate whether effects might be different for caregivers not asking for or considering this type of support. Also, there is a high probability that caregiver/care-recipient dyads in the intervention group with lower socioeconomic status and lower educational level will be underrepresented because Baluchonnage is normally a rather expensive service that is not commonly known in Belgium. Nevertheless, we will use statistical techniques, such as propensity score matching, to respond to this problem. Also, the fact that participants receive the in-home respite care five days for free can also reduce the gap in socioeconomic status between intervention en control group.

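### Matching cannot balance earlier Baluchon use, which only the intervention group may have, or reason for respite, which controls give only at six months, yet the matched effect is called unbiased

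*Protocol article*

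**What the plan says.** **Earlier use.** Study participants sets different rules for the two groups. For controls: "dyads of the control group must never had in-home respite of the Baluchon type, but be eligible and willing to receive it". For the other group: "dyads from the intervention group who have already received in-home respite care from the Baluchon type in the past are still allowed". The section on the control group repeats the exclusion. Recruitment confirms that intervention dyads may be requesting either their first Baluchon stay or a further one.

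**Reason for respite.** Background characteristics states: "In both study groups the reason for (potential) use of respite will be asked". The timing is given only in the tables under Research outcomes and instruments. The row "Reason for respite" is marked at baseline (T0) in Table 1 for the intervention group, and only at T0 + 6 months (T2) in Table 2 for controls. Data collection names six months as the primary endpoint.

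**The claim.** After introducing propensity score matching, Statistical analysis says: "In this way we can expect the observed effect to be an unbiased estimate of the real effect". The Discussion repeats it among the strengths: "the found intervention effects can be considered unbiased estimates of the real effect". The limitations then concede that "there can still be unmeasured confounders influencing causal inference". They also expect dyads already familiar with the service to respond differently from first-time users, and for this they say only that subgroup analyses may be done.

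**The concern.** Matching can balance only characteristics that occur in both groups and are measured before treatment in both. Earlier Baluchon use fails the first condition because of the eligibility rules. Reason for respite fails the second because of the data collection schedule.

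For a returning user, the baseline ZBI may already reflect earlier respite, so matching on it does not necessarily match on an untreated starting point. Followed as written, the plan pools these dyads with first-time users, compares the mixture with never-users, and describes the result as unbiased. The Discussion links the findings to possible reimbursement, so that description could be carried into policy advice that the design does not support.

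**Working it through.** **1. The plan's own sample size.** Inputs from Sample size: difference 6 ZBI points, SD 15 (effect size 0.4), power 80%, significance level 0.05 (taken as two-sided), drop-out 20%.

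- n per group = 2 × (1.960 + 0.842)² / 0.4² = 98.1, rounded up to 99.
- With drop-out: 99 / 0.8 = 123.75, rounded up to 124.
- Controls: 2 × 124 = 248.

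The stated 124 and 248 reproduce. An exact t-test calculation gives 99.08, hence 100 and then 125, which is an immaterial difference. The size is a 1:1 calculation, with controls then doubled to allow matching.

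**2. Overlap on earlier use.** By eligibility, P(control | earlier use) = 0. If the propensity model includes earlier use, returning users have no possible match. If it omits it, they are matched to never-users. No choice of covariates changes this, because it is fixed by who may enter each group.

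**3. Timing of reason for respite.**

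| Group | T0 | T2 (primary endpoint) |
|---|---|---|
| Intervention (Table 1) | recorded | not recorded |
| Control (Table 2) | not recorded | recorded |

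The Table 2 row does not look like a damaged table. The row just above it, on preparedness to receive the service, is marked at T0, and the willingness-to-pay row shows the same pattern of a blank T0 and a mark at T2. The only control value is therefore taken together with the six-month outcome.

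**4. Possible shift in the primary contrast.** Let p be the share of returning users and g the difference in six-month ZBI between returning users and comparable first-time users. The pooled contrast shifts by p × g. Neither value is in the documents; both are assumed.

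| p | g = 2 | g = 4 | g = 6 |
|---|---|---|---|
| 10% | 0.2 | 0.4 | 0.6 |
| 30% | 0.6 | 1.2 | 1.8 |
| 50% | 1.0 | 2.0 | 3.0 |

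The direction is unknown.

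**5. Power if only first-time users are compared.** Evaluable first-time users = 124 × 0.8 × (1 − p). Power is from the two-sample t-test at effect size 0.4, two-sided 0.05, assuming every first-time user is matched and taking no gain from baseline adjustment.

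| p (assumed) | Evaluable | 1:1 matching | 1:2 matching |
|---|---|---|---|
| 0% | 99.2 | 80% | 90% |
| 10% | 89.3 | 76% | 87% |
| 20% | 79.4 | 71% | 83% |
| 30% | 69.4 | 65% | 77% |
| 40% | 59.5 | 58% | 71% |
| 50% | 49.6 | 51% | 63% |

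Evaluable controls number 248 × 0.8 = 198.4, which is enough for 1:2 matching in every row.

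**The case against.** The strongest reply is that the article is condensed and candid. A propensity covariate list and firm subgroup definitions commonly belong in an analysis plan. Earlier use is recorded at T0, so a first-time-user analysis needs no new data. The limitations admit both unmeasured confounding and a different response in returning users. The low end of the assumed shift, 0.2 points, is negligible against 6.

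Much of this stands, but it does not settle the point. An unseen covariate list cannot create overlap that eligibility rules out, nor supply a baseline answer that controls were never asked for. The admitted limitations contradict the unbiasedness statements and do not cure them. The subgroup analysis is optional and leaves the main contrast unchanged.

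A reader might infer more than the documents support:

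- *That the propensity score is the only protection against confounding.* Controls must also be eligible for and willing to receive the service, and their preparedness is recorded at T0. The article also names matching as one example of the techniques to be used.
- *That returning users are satisfied customers, or that earlier use and reason for respite strongly determine the choice of Baluchon.* The documents mention familiarity and trust, but give neither satisfaction among returning users nor the strength of either factor.
- *That a large, known fraction of the intervention group lacks a comparator.* The share is not stated.
- *That power in the restricted analysis stays near 80% because all controls can be used.* Comparing first-time users with all 198 or so evaluable controls gives about 82% at p = 30%, but the plan is to match.

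**Conclusion.** The point holds as a structural fault and a wording fault. Earlier use cannot be balanced under the eligibility rules, and reason for respite cannot be used as a baseline covariate under the schedule. The two statements that the matched effect is unbiased are therefore wrong as written, and they conflict with the limitations in the same article.

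The size of any bias cannot be determined from the documents. The range of 0.2 to 3.0 ZBI points rests wholly on assumed shares of 10% to 50% and assumed differences of 2 to 6 points, and it could go either way. It does not follow that the all-comers comparison must be abandoned: the trial deliberately recruits both first-time and returning users, and that result can still be reported provided it is not described as unbiased.

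**What to change.** 1. **Move one item.** Ask controls their reason for potential respite at the T0 home visit that is already planned, and correct Table 2. It is then available as a baseline covariate. For controls it remains a hypothetical reason, so the move repairs the timing but not that difference. It has to be done prospectively.
2. **Fix one analysis in advance.** Make first-time users versus never-users a mandatory, pre-specified propensity-matched analysis of the primary outcome, reported beside the all-comers result and using the earlier-use item already collected at T0. Report returning users separately and descriptively.
3. **Change the wording.** In Statistical analysis and Discussion, state that the estimate is unbiased only if all confounders are measured and balanced, and that this does not hold for earlier Baluchon use.

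The cost is one question moved, some text, and lower power in the restricted analysis, as tabulated above. No extra enrolment is needed, and the two analyses need not be required to agree before a result is reported.
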